## Abstract

**Introduction:**

There is a lack of prospective studies comparing Roux-en-Y gastric bypass (RYGB) and one-anastomosis gastric bypass (OAGB). Also, the effects of bariatric surgery and weight loss need a deeper understanding through metabolic studies. We describe the trial protocol and interim analysis of a prospective randomized controlled study comparing RYGB and OAGB: the RYSA trial.

**Materials and methods:**

In total, 120 bariatric patients will be randomized between RYGB and OAGB in two academic centers. All patients will be followed up for 10 years with analysis and measurements of weight, comorbidities, blood tests, body composition and questionnaires. Extensive metabolic analyses (mixed meal tests, energy expenditure, biopsies of muscle and subcutaneous fat, urine, saliva and fecal samples) will be carried out in the Obesity Research Unit, University of Helsinki, for all patients treated at the Helsinki University Hospital (80 patients) at baseline, 6 months and 12 months. Bile reflux will be studied for the OAGB group at the Helsinki University Hospital at 6 months with gastroscopy and scintigraphy.

**Results:**

At an interim analysis at 3 months (half-way) through recruitment (30 RYGB and 30 OAGB patients) there have been no deaths and no intensive care unit admittances. One patient in both groups required additional gastroscopy, with anastomosis dilatation in the RYGB group but with no additional intervention in the OAGB group.

**Conclusion:**

The trial can be safely carried out. Recruitment is estimated to be complete by the end of 2019.

**Trial registration:**

Clinical Trials Identifier NCT02882685. Registered on August 30th 2016.

## Introduction

Surgery is the most effective treatment for morbid obesity, and gastric bypass has been considered a gold standard [1, 2]. Currently there are several viable options for performing a gastric bypass. Roux-en-Y gastric bypass (RYGB) has been modified from the bypass method published by Mason and Ito in the 1960s [3]. The hallmarks of RYGB are a small gastric pouch anastomosed to an alimentary limb and a separate biliopancreatic (BP) limb [4]. In 2001 Rutledge published a technique called mini-gastric bypass (MGB; later termed one-anastomosis gastric bypass (OAGB) or single-anastomosis gastric bypass (SAGB)) with a longer tubular-shaped pouch and a longer BP limb anastomosed directly into the distal end of the gastric pouch [5]. Since then, and according to the International Federation for the Surgery of Obesity and Metabolic Disorders 2018 statement on MGB/OAGB/SAGB procedures, a preferred term for all bypasses with a long gastric pouch and a long BP limb should be OAGB [6].

RYGB and OAGB have both shown excellent weight-loss results in many cohort series and prospective trials [7–9]. However, to our knowledge only two prospective randomized controlled trials comparing RYGB and OAGB have been published [10, 11]. It has been stated that OAGB would be at least as effective, faster to perform and less prone to complications such as internal herniations compared to RYGB [12]. On the other hand, it has been suggested that OAGB can cause bile reflux, a potential risk for premalignant Barrett’s metaplasia of the esophagus. OAGB has been proposed to have a more favorable effect on type 2 diabetes mellitus (T2DM) but might be more prone to nutritional deficiencies [6, 11]. The BP limb is usually longer in OAGB compared to RYGB, which most likely affects T2DM remission, but limb lengths have not been standardized in either procedure. Overall, there are a lot of unanswered questions when comparing RYGB and OAGB. A recent meta-analysis on this subject concluded that a larger sample size and multicenter randomized controlled trials are needed to compare the effectiveness and safety between these procedures [13].

Bariatric surgery induces changes in the entire body including body composition, bile acid metabolism, energy expenditure, cellular metabolism, gut microbiota, chronic stress, vitamin and electrolyte homeostasis, glucose tolerance and lipid metabolism, as well as eating behavior, physical activity, self-image, social relationships and quality of life. The mechanisms of these changes are not fully understood, and neither are the differences in the underlying mechanisms of RYGB and OAGB. A comprehensive approach to obesity management is needed in order to be able to tailor a treatment for each patient.

Our objective is to compare outcomes of RYGB and OAGB procedures and to study comprehensively all changes in obesity-related conditions in a prospective study where we randomize between RYGB and OAGB.

Here we describe the trial protocol for a randomized controlled trial, the Roux-en-Y Gastric Bypass vs Single-Anastomosis Gastric Bypass (RYSA) trial, with an interim analysis regarding safety and trial progression.

## Materials and methods

### Aims of the study

The primary outcome is weight loss 2 years after the operation. Weight loss is measured as percentage excess weight loss (%EWL) and percentage total weight loss (%TWL). %EWL is calculated as a percentage of lost excess weight since the preoperative visit compared to an ideal weight with a body mass index (BMI) of 25 kg/m^2^. Weight loss will also be analyzed as a grouping variable according to different categories of weight loss to compare responders and nonresponders to bariatric surgery. For EWL% we use the categories 0–24.99%, 25–49.99%, 50–74.99% and ≥75%, and for TWL% we use the categories <10%, 10–19.99%, 20–29.99%, 30–39.99%, ≥40% to determine participants with different amounts of weight loss achieved.

The secondary outcomes to be measured at the time points of 6 months, 12 months, 24 months, 5 years and 10 years are as follows:
Weight loss (%EWL, %TWL)Complications (any complication requiring any intervention or a prolonged hospital stay or additional outpatient visits)Perioperative factors (operation time, hospital stay, nausea, ability to take fluids and mobilization)Remission of comorbidities (including, for example, T2DM, hypertension, nonalcoholic fatty liver disease); remission is defined as normalization of measured values without medicationChanges in nutritional, metabolic and safety laboratory parameters (e.g., hemoglobin, vitamins, albumin, electrolytes, liver enzymes, lipids)Glucose tolerance and insulin response during an oral glucose tolerance test (OGTT) or meal testContinuous glucose monitoring (CGM)Changes in body composition (whole body fat with dual-energy x-ray absorptiometry (DEXA) and bioelectrical impedance (BIA), lean mass (DEXA and BIA), bone mineral mass and density (DEXA), subcutaneous fat (magnetic resonance imaging (MRI)), intra-abdominal fat (MRI), liver fat (magnetic resonance spectroscopy (MRS))Bile reflux at 6 months (for the OAGB group at Helsinki University Hospital (HUH))Tendency for urolithiasisChanges in cortisol and other hormone metabolismChanges in blood and tissue (adipose tissue, muscle) transcriptomics, proteomics, metabolomicsChanges in tissue (adipose tissue, muscle) mitochondrial activitiesChanges in gut and saliva microbiota and bile acid metabolismChanges in quality of life and lifestyle and gastrointestinal symptoms

Drop-out and lost-to-follow-up patients will be included in the analyses with measurements and values that have been obtained prior to drop-out. A 10% drop-out rate has been included in the power calculation regarding the primary outcome. Patients are regarded as part of their original treatment group according to randomization on an intention-to-treat basis.

An interim analysis regarding safety and trial progression has been performed after half of the patients have been randomized and undergone surgery.

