### Sample size

This study is designed as a superiority trial based on previous cohort series. According to power calculations finding a difference of 10 in %EWL with the assumptions of mean %EWL = 60 (standard deviation (SD) = 17) in the RYGB group, with alpha = 0.05, 50 patients in each group would be sufficient to reach the power of 80%. If a drop-out of 10% is taken into account, this would mean 55 patients per group. Power calculations were performed by simulation using the Mann-Whitney-Wilcoxon test (PASS v13.0, NCSS Inc., Kaysville, Utah, USA). Since there was a lack of published data on comparisons between these two operations at the time of designing the study, we decided to recruit 60 patients for both treatment groups in order to have sufficient statistical power regarding the primary end point (10% difference in %EWL at 2 years between the groups).

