### Statistical analyses

Normally distributed variables will be expressed as the mean and SD, and non-normally distributed variables will be expressed as the median and interquartile range; categorical variables will be expressed as the number and percentage.

To test the group differences (OAGB vs RYGB) in the primary and secondary endpoints, we will use the Student’s *t* test for continuous normally distributed variables, the Mann–Whitney *U* test for continuous non-normally distributed data, and the chi-squared test or Fisher’s exact test for categorical variables. Additionally, we will conduct multivariable analysis with generalized mixed linear regression or logistic regression models with adjustment for possible confounding factors. The statistical analyses will be conducted on an intention-to-treat basis. A *P* value < 0.05 will be considered statistically significant.

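### The protocol defines the primary endpoint in two ways: %EWL and %TWL together in the aims, %EWL alone in the sample size section

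*Protocol article*

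**What the plan says.** All references are to the protocol article.

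- **Aims of the study, primary outcome.** "The primary outcome is weight loss 2 years after the operation". The next sentence reads "Weight loss is measured as percentage excess weight loss (%EWL) and percentage total weight loss (%TWL". No order is given, and response categories follow for both measures.
- **Aims of the study, secondary outcomes.** The list is headed by time points that include 24 months, and its first item is "Weight loss (%EWL, %TWL". The 24-month result on each measure is therefore listed as secondary as well.
- **Sample size.** The calculation is for "finding a difference of 10 in %EWL", assuming "mean %EWL = 60 (standard deviation (SD) = 17) in the RYGB group". The section closes by referring to "the primary end point (10% difference in %EWL at 2 years between the groups". %TWL does not appear, and no %TWL effect or SD is given anywhere.
- **Statistical analyses.** One set of tests covers primary and secondary endpoints alike, and a P "value < 0.05 will be considered statistically significant".
- **Study sites and randomization.** The trial is open-label, and outcomes are analysed without blinding.

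**The concern.** Identifying the primary endpoint is the protocol's own task, and two of its sections give different answers. On the aims section alone, %EWL and %TWL have equal standing. On the sample size section alone, %EWL is the endpoint. The secondary list then places the same 24-month %EWL result in a second tier.

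The measures are not interchangeable. %EWL divides the loss by the excess over BMI 25, and %TWL divides it by total weight, so a chance imbalance in baseline BMI moves them differently. One can be significant when the other is not. The trial is meant to show superiority and its outcomes are analysed unblinded. An unresolved definition therefore lets the headline measure be chosen after the results are known, and readers could not tell whether it had been.

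**Working it through.** **1. The plan's own figure.** Inputs from the sample size section: difference 10, SD 17 (taken as equal in both arms), alpha 0.05, power 80%, Mann-Whitney-Wilcoxon test. Sidedness is not stated.

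- Two-sided normal formula: n = 2 × [17 × (1.960 + 0.842) / 10]² = 45.4, so 46 per group. A one-sided test gives 36, which does not match the plan.
- The t-test n of 46.3, divided by the Mann-Whitney efficiency 3/π = 0.955, gives 48.5, so 49.
- Simulated Mann-Whitney power at 50 per group (20,000 runs, normal data) is 80.8%.

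The stated 50 per group is reproduced, for %EWL, two-sided. With 60 recruited and 10% drop-out there are 60 × 0.9 = 54 completers per group, and simulated Mann-Whitney power for %EWL is about 84%.

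**2. How the measures are linked.** With ideal weight set at BMI 25 and the same baseline weight for both,

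%EWL = %TWL × BMI / (BMI − 25).

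The multiplier is 44.5/19.5 = 2.28 at BMI 44.5, but 38/13 = 2.92 at BMI 38 and 50/25 = 2.00 at BMI 50. The measures are strongly related but not identical.

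**3. False-positive rate if either measure may carry the claim.** For two two-sided 5% tests with correlation r, the rate is 1 − P(|Z₁| < 1.96 and |Z₂| < 1.96):

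| r | rate |
|---|---|
| 0 | 9.75% |
| 0.7 | 8.3% |
| 0.8 | 7.8% |
| 0.9 | 7.0% |

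The documents do not give r, so it was simulated. Baseline BMI was about 44.5, SD about 5.7 (midway between the two arms in the interim results), with values kept at 35 or above. There were 54 completers per arm and a mean %EWL of 60. Two assumptions were added: %TWL is independent of BMI, and its SD is 4 to 8 points. Results with no true difference (t tests, 20,000 runs each):

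| assumed %TWL SD | implied %EWL SD | r | either test P < 0.05 | tests disagree |
|---|---|---|---|---|
| 4 | 13.9 | 0.68 | 8.5% | 6.9% |
| 5 | 15.6 | 0.76 | 7.9% | 6.1% |
| 6 | 17.5 | 0.81 | 7.4% | 5.2% |
| 7 | 19.6 | 0.85 | 7.3% | 4.8% |
| 8 | 21.7 | 0.88 | 7.4% | 4.5% |

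A repeat with a different random seed gave 7.2% to 8.5% in the fourth column.

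**4. Disagreement under the planned effect.** With a true 10-point %EWL difference and a %TWL SD of 5 to 8, the two tests fell on opposite sides of 0.05 in roughly 9–16% of simulated trials. The repeat, which added the effect as a constant %TWL shift of 10/2.37 = 4.2 points, gave 10% at SD 5, 15% at SD 6 and 17–18% at SD 7–8. At SD 7–8 the implied %EWL SD is about 20–22, above the plan's 17. Interpolating to the plan's SD of 17 gives about 14%.

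**The case against.** The strongest reply is that the sample size section already settles the matter. The aims section states one outcome, weight loss, and then how it is measured; it never uses the term co-primary. The sample size section then identifies the end point as %EWL. Read together, %EWL decides, there is one primary test, and the error rate is 5%. The repeated 24-month entry comes from a single time-point header covering the whole secondary list, which also includes perioperative factors, so it is loose drafting. An unseen analysis plan may also rank the measures.

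Much of this stands. The sample size section does point to %EWL, and the absence of a multiplicity rule from a condensed article is no finding. But that section does not say %TWL is secondary, and an analysis plan would not remove the conflict between the two sections.

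Two stronger inferences are tempting and are not supported:

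- *That the trial, followed as written, wins if either measure is significant, so the 5% level is already broken.* No such rule is written. If %EWL alone decides, the rate is 5%; if both must succeed, it is at most 5%.
- *That formally controlling both measures would push power below 80%.* At 2.5% with 54 completers, power is 78% (t test) or 76% (Mann-Whitney), but this is for %EWL taken alone. If either could win at 2.5% each, the chance of winning on at least one was about 82–98% in simulations with a %TWL SD of 5 to 7.

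**Conclusion.** The contradiction is real and lies in the article's own text: the aims section gives the primary outcome two unranked measures and repeats both as secondary, while the sample size section names and powers one.

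Its size is conditional. If the ambiguity were used so that either measure could be presented as primary, the false-positive rate would be about 7–8.5% rather than 5%. With a true 10-point effect, roughly one trial in ten to one in six would give different answers on the two measures (about 14% at the plan's SD). These figures assume two-sided tests, normal data, 54 completers per arm, the interim BMI distribution, %TWL independent of BMI and a %TWL SD of 4–8 points (5–8 for disagreement under the effect). The contradiction itself depends on none of these assumptions.

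**What to change.** Before any 24-month comparison between the arms, bring the aims section into line with the sample size section:

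- State that %EWL at 24 months is the single primary endpoint, tested at two-sided alpha 0.05.
- State that %TWL at 24 months is secondary and cannot by itself support a claim of superiority.
- Remove 24-month %EWL from the secondary list, leaving its other time points there.

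The cost is a few lines of text. Sample size, alpha and the stated 80% power are unchanged, because the calculation was already for %EWL alone. The only downside is that a significant %TWL result without a significant %EWL result could no longer carry the trial.

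### The drop-out rule does not fit a single-value 24-month test: it either lets earlier weights stand in for the 2-year value or leaves a completers-only comparison

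*Protocol article*

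**What the plan says.** The protocol article, under Aims of the study, fixes the endpoint at one time point: "The primary outcome is weight loss 2 years after the operation", measured as %EWL and %TWL. The same section gives the rule for drop-out and loss to follow-up: such "patients will be included in the analyses with measurements and values that have been obtained prior to drop-out". The next two sentences add that "A 10% drop-out rate has been included in the power calculation regarding the primary outcome" and that "Patients are regarded as part of their original treatment group according to randomization on an intention-to-treat basis".

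Under Statistical analyses, the two arms are compared on primary and secondary endpoints by Student's t test or the Mann–Whitney U test for continuous data. Mixed linear or logistic regression is listed as an additional analysis, to adjust for confounders. The section also states: "The statistical analyses will be conducted on an intention-to-treat basis".

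Under Sample size, 50 patients per group are enlarged to 55 for 10% drop-out, and 60 per group are to be recruited.

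**The concern.** A two-sample test at 24 months uses one number per patient. For someone who left at 6 months, that number does not exist. The drop-out sentence says the person is included with what was measured before leaving, and in this test that can only mean that an older weight takes the place of the 2-year weight. %EWL is counted from the preoperative visit, where patients are also randomised, about 8 weeks before surgery. A patient who leaves before any postoperative weight would therefore enter at %EWL = 0.

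Weight after bypass changes over the first two years, so an older value is not a 2-year value, and the error depends on when the patient left. If drop-out differs between arms in number or timing, the error does not cancel. The trial is open-label and outcomes are analysed without blinding, so which analysis is meant should be settled before 24-month data are examined.

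**Working it through.** **The plan's own figure.** The inputs under Sample size are "finding a difference of 10 in %EWL", "mean %EWL = 60 (standard deviation (SD) = 17) in the RYGB group", alpha 0.05 and 80% power by simulated Mann–Whitney test. Two-sided testing and SD 17 in both arms are assumed.

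- Normal approximation: n = 2 × (1.96 + 0.84)² × (17/10)² ≈ 45.3, so 46 per group.
- Mann–Whitney under normality: 46 / (3/π) = 48.2.
- Simulated Mann–Whitney power at 50 per group (20,000 runs): 0.81.
- Drop-out: 50 × 1.10 = 55; dividing instead, 50 / 0.90 = 55.6, so 56.

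The stated 50 and 55 reproduce to within a patient or two. With 60 per group and 10% lost, 54 remain. Simulated completers-only power is then about 0.84, and the estimated difference is 10.0 if drop-out is unrelated to outcome.

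**Bias if earlier values stand in.** Let d₁ and d₂ be the drop-out proportions in RYGB and OAGB, and g₁ and g₂ the amounts by which the carried value falls short of the 24-month value. The bias in the difference (OAGB minus RYGB) is d₁g₁ − d₂g₂. The documents give neither the split nor the gap, so both are assumptions.

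- Different numbers, same gap (5% v 15%): (0.15 − 0.05) × 10, 20, 30 = 1, 2, 3 points in size, or 10 to 30% of the target difference.
- Same numbers, different timing (10% each, gaps 10 and 30): 0.10 × (30 − 10) = 2 points.
- Same numbers, same gap: each arm mean is off by 0.10 × 10 to 0.10 × 30 = 1 to 3 points, but this cancels in the difference.

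**Carried value as a fraction of the 24-month value.** This version uses 60 per arm, true means 60 and 70, and SD 17. The expected arm mean is μ × [1 − d × (1 − fraction)]. For example, at fraction 0.5 with 5% v 15%: 60 × 0.975 = 58.5 and 70 × 0.925 = 64.75, a difference of 6.25. Simulated estimates of the true 10-point difference, with Mann–Whitney power in brackets:

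| Drop-out, RYGB / OAGB | Fraction 0 (baseline only) | 0.5 | 0.75 | 1.1 |
|---|---|---|---|---|
| 10% / 10% | 9.0 (0.74) | 9.5 (0.79) | 9.7 (0.85) | 10.1 (0.88) |
| 5% / 15% | 2.5 (0.30) | 6.3 (0.42) | 8.1 (0.69) | 10.7 (0.91) |
| 15% / 5% | 15.5 (0.96) | 12.8 (0.96) | 11.4 (0.95) | 9.4 (0.83) |

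With no true difference (both means 60) and a 5% v 15% split, the bias is about 6.0, 3.0, 1.5 and 0.6 points in size across the same fractions. Type I error is about 0.12, 0.10, 0.07 and 0.05. At fraction 1.1 (a value carried from a lower weight, before regain) the bias changes sign.

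**Standard error.** Assume 10% carried values and SD 17 among both carried and observed values. The variance per arm is 289 + 0.10 × 0.90 × g², and the SE of the difference with 60 per arm is √(2 × variance / 60).

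- g = 10: variance 298, SE 3.15.
- g = 20: variance 325, SE 3.29.
- g = 30: variance 370, SE 3.51.
- Completers, 54 per arm: √(2 × 289 / 54) = 3.27.

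**The case against.** The strongest reply is that the plan never states carry-forward. The sentence covers all analyses, and outcomes are planned at several visits. A drop-out can be included at the visits attended, or through the additional mixed model, without any early weight entering the 2-year test. The allowance for 10% drop-out on the primary outcome supports this, since it treats drop-outs as lost to that test; under carry-forward it would be largely unnecessary. The intention-to-treat sentence concerns allocation and does not promise a 24-month value for everyone. Details of imputation also commonly sit in an analysis plan, which is not shown.

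Much of this stands. A reader might infer that last observation carried forward is the specified method; the text permits it but does not say so. Nor does a completers-only test plainly contradict intention to treat as the article describes it. What remains is that the drop-out sentence is a stated rule, not a missing detail. In the stated primary test it cannot be followed without substituting an older value, and the reading that avoids substitution does not include drop-outs in that test.

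Three further inferences are not supported:

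- That carry-forward makes the standard error too small. Compared with completers, it is smaller at a 10-point gap but larger at 20 and 30 points.
- That 3-month weights would be carried. The follow-up section describes laboratory tests and medication review at that visit, with telephone contact at Oulu, and mentions no weight.
- That early remission of comorbidities is carried to later years. No text says this.

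**Conclusion.** The concern holds as a mismatch between the drop-out rule and the primary test. The article allows two different 24-month analyses, one with older weights standing in and one restricted to completers, and does not say which is meant.

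Under carry-forward, the bias is about 1 to 3 %EWL points for an assumed 5% v 15% drop-out and a 10 to 30 point gap. It is larger if patients leave with only a baseline weight. With balanced drop-out the difference stays at 9.7 to 10.1 when the last value is 75% to 110% of the 24-month value, and falls to 9.0 only when baseline values are carried. The harm therefore depends on imbalance or very early loss, neither of which the documents predict or rule out. The calculation of 50 and 55 per group is not affected.

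**What to change.** Replace the drop-out sentence with a rule for the 24-month contrast:

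- Estimate the treatment difference at 24 months from a repeated-measures mixed model on %EWL at 6, 12 and 24 months, with treatment by visit and adjustment for centre and diabetes, the allocation strata.
- Include every randomised patient with a post-baseline weight in the arm assigned. A patient seen only at 1 month contributes only if that visit is added to the model, so the text should say whether it is.
- State that no value is carried forward to a later visit.
- Add one sensitivity analysis for data not missing at random, for example multiple imputation with a shift for drop-outs. It should also cover patients with no postoperative weight.

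The 6- and 12-month weights are already scheduled and mixed models are already named, so no new data are needed. The cost is a change of wording and slightly more analysis work. The mixed model would replace the two-sample test as the primary analysis, and it relies on drop-out being explained by the observed weights and covariates, which is why the sensitivity analysis is needed.
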